### Outcome Measures

#### Primary Outcomes

The primary outcomes are the changes in trajectories of mental health, primarily anxiety at baseline (week 0) until final assessments (week 26) between 6 months after invitation to the WTC intervention or usual care. The trajectories are also measured biweekly with short follow-ups at different time points from week 2 until week 26. We will use multilevel modeling to describe within-person differences in anxiety and depression at different time points. We will compare the observed trajectory with those of the control group. Interactions by demographic subgroups (primarily age, gender, race, and socioeconomic status) will be assessed for identification of potential effect modifications. 

#### Secondary Outcomes

An economic analysis will be conducted by comparing incremental costs and health outcomes for the Wellbeing Tracker and WTC compared to within-person expected trajectories using a cost-effectiveness acceptability curve. These costs will be based on the costs associated with the ongoing recruitment and maintenance costs of WTC compared to the cost per QALY gained through the use of these interventions [20]. To be somewhat comparable with World Health Organization’s standards for ranking public health interventions, the determination of whether the WTC overall is highly cost-effective will be based on a threshold of CAD $124 (~US $100) per QALY gained [21]. QALYs will be estimated using the SF-6D (Short-Form Six-Dimension), calculated on the basis of the SF-12 (12-item Short Form Survey) [21]. This analysis will provide an empirical basis for the effect of allocation of health care resources in Canada. To aid other countries, we will also base cost-effectiveness calculations based on estimations that incorporate implementation costs of the Wellbeing Tracker and WTC. We will also estimate cost-effectiveness based on clinically Reliable Change Index scores (ie, 5 points on the PHQ-9 [22] and a 6-point change on the GAD-7 [23], as well as employment status. The schedule of the Let’s Act on Mental Health study is outlined in Table 1.

**Table 1 table1:** Schedule of the Let’s Act on Mental Health Survey of 2022.

Procedures	Study period (day 1 to week 26)						
Enrollment	Day 1	Week 0	Week 1	Weeks 2 and 4	Week 6	Weeks 8-24	Week 26
Eligibility screening	✓						
Informed consent	✓						
Screening assessments (PHQ-9^a^ item 9)	✓						
Drug use (DUDIT-C modified^b^)	✓						✓
Problematic alcohol use (AUDIT-C^c^)	✓						✓
Enrollment							
Demographics		✓					
3-Digit postal codes		✓					
Baseline with self-reported questionnaires (GAD-7^d^, PHQ-4^e^, Current Substance Use, SF-12^f^, and WSAS^g^)		✓					
Randomization to the WTC^h^ intervention or usual care group through an email invitation			✓				
Biweekly short and long follow-up (GAD-7, PHQ-4, Current Substance Use, SF-12, and WSAS)				✓		✓	
WTC and usual care monitoring for contamination and compliance checks					✓		✓
Final assessment (GAD-7, PHQ-4, current substance use, SF-12, and WSAS)							✓

^a^PHQ-9: 9-item Patient Health Questionnaire.

^b^DUDIT-C modified: modified Drug Use Disorders Identification Test.

^c^AUDIT-C: Alcohol Use Disorders Identification Test.

^d^GAD-7: 7-item Generalized Anxiety Disorder Scale.

^e^PHQ-4: 4-item Patient Health Questionnaire.

^f^SF-12: 12-item Short Form Survey.

^g^WSAS: Work and Social Adjustment Scale.

^h^WTC: Wellness Together Canada.

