## Methods

### Trial Design

The Let’s Act on Mental Health study is a longitudinal, fully remote, equally randomized (1:1), double-blind, alternative intervention–controlled, parallel-group randomized controlled trial to be conducted between October 2023 and April 2024 with a prospective follow-up for 26 weeks. This trial will evaluate whether digital interventions such as WTC improve population mental health trajectories over time. The trial will consist of 1 baseline assessment at week 0, 13 biweekly short and long follow-ups from week 24, intervention monitoring twice at weeks 6 and 26, and 1 final assessment at the end of the 26-week follow-up period. An overview of the trial process is shown in Figure 1.

The study’s overall objective is to evaluate the effectiveness and cost-effectiveness of the WTC portal by conducting a randomized controlled trial. We will use a “Knowledge-to-Action Framework” [14] with extensive stakeholder and cross-sectoral engagement and will incorporate program elements with people with lived experience.

The research questions we seek to answer with this study are the following: (1) how effective is the WTC portal in altering the trajectories of mental health and substance use, primarily anxiety, compared to usual care? (2) What is the benefit of WTC versus usual care in terms of incremental costs, health outcomes, ongoing recruitment, and maintenance costs compared to the cost per quality-adjusted life year (QALY) gained using these interventions? (3) What is the differential impact of WTC by age, sex or gender, race, and socioeconomic status?

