### Intervention

The intervention group will be invited to the WTC portal, which provides options for digital interventions. A single-sign on system used by WTC will be used to facilitate ease of transfer.

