## Discussion

### Anticipated Findings

At baseline, with regard to gender and race, a greater proportion of participants are female (n=359, 75.57%) and White (n=335, 67.95%). We aim to generalize this study to the Canadian population; hence, we have been weighting samples at the census level based on gender and province to make this study representative. Weighing of the sample will help us understand how generalizable the sample and advertisements are and whether they are adequately representative. The SF-12, measuring mental and physical health, has revealed a significant decline in mental health from baseline to short and long follow-ups in this study. It is too early to discuss how this will develop longitudinally, but the preliminary results suggest a larger decline in mental health than in physical health in the Canadian population.

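### The economic analysis is specified against within-person expected trajectories and an undefined Wellbeing Tracker, so as written it does not answer the randomised WTC-versus-usual-care question

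*Protocol article*

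**What the plan says.** In Trial Design, the protocol article states that its "overall objective is to evaluate the effectiveness and cost-effectiveness of the WTC portal by conducting a randomized controlled trial". Research question 2 in the same section begins "What is the benefit of WTC versus usual care in terms of incremental costs, health outcomes", and the end of the Introduction gives the same aim. The Intervention and Control sections describe two arms only. On one side, "The intervention group will be invited to the WTC portal, which provides options for digital interventions"; on the other, participants are referred to the self-care tools on the CAMH website.

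Secondary Outcomes describes the economic analysis as "comparing incremental costs and health outcomes for the Wellbeing Tracker and WTC compared to within-person expected trajectories", summarised by an acceptability curve. Its cost inputs are the "costs associated with the ongoing recruitment and maintenance costs of WTC", with a further calculation, meant for other countries, that adds implementation costs of the Tracker and WTC. QALYs come from the SF-6D, derived from the SF-12. Neither usual care nor the control group is mentioned in this description.

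**The concern.** The comparator determines what an incremental cost per QALY means. Research question 2 fixes it as usual care, and randomisation supplies a concurrent group that received it. The section meant to answer that question names a different comparator and adds a product to which nobody is randomised.

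An analyst following the section literally would report a ratio without the protection of randomisation. Whatever happens to utility over 26 weeks for reasons unrelated to treatment could enter the QALY difference. With no control-arm cost, the incremental cost would in effect treat usual care as free. Cost-effectiveness is half of the stated overall objective, and the result is meant to inform resource allocation in Canada, so the comparator should not be left in conflict.

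**Working it through.** The plan states no figure to reproduce here. The check is a comparison of sections, followed by an illustration.

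**1. Comparator.**
- Trial Design, research question 2: WTC versus usual care.
- Introduction and Trial Design: cost-effectiveness evaluated by the randomised trial.
- Secondary Outcomes: participants' own expected trajectories.
- Primary Outcomes and Statistical Analysis: these do name the control group, but for the anxiety and depression trajectories, not for costs or QALYs.

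The article therefore states a conflicting comparator; it does not simply leave one out.

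**2. Interventions evaluated.** Intervention, Control and Sample Size give two arms of 1000. The Wellbeing Tracker appears twice, both times in Secondary Outcomes, and is not defined, allocated or scheduled anywhere.

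**3. Costs.** Incremental cost per person is C(WTC) - C(control). The section names costs for WTC and the Tracker and none for usual care. Leaving C(control) out sets it to zero and overstates the increment by C(control). The article gives no value, so the size is unknown.

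**4. What a within-person expectation can rest on.** Table 1 places SF-12 at week 0 and randomisation at week 1. There is one utility value per participant before randomisation, and a single value gives no pre-intervention slope. Built from a participant's own data alone, the expectation reduces to baseline carried forward. Any other form needs control-arm or external data, and the section names neither.

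**5. Illustration (utilities assumed, because the article gives none).** For a linear change d in utility over 0.5 year, the QALY change from baseline carried forward is 0.5 × d × 0.5 = 0.25d.
- WTC, d = -0.01: 0.25 × (-0.01) = -0.0025. This is the baseline-anchored result.
- Control, d = -0.02: 0.25 × (-0.02) = -0.0050.
- Between arms: -0.0025 - (-0.0050) = +0.0025.

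The two results differ by 0.25 times the control-arm change. For an assumed treatment-unrelated drift of 0.01 to 0.05 in either direction, the shift is 0.25 × 0.01 = 0.0025 to 0.25 × 0.05 = 0.0125 QALY per person. A concurrent randomised control cancels this in expectation.

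**6. Is drift plausible?** Anticipated Findings says the SF-12 "has revealed a significant decline in mental health from baseline to short and long follow-ups in this study". That is the instrument from which the QALYs are derived.

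**7. Can the randomised comparison be made?** Table 1 schedules SF-12 at baseline, follow-ups and week 26 with no restriction by arm, so the outcome data for it are already planned.

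**The case against.** The strongest reply is that the expected trajectory is undefined. It could be a model-predicted path that already contains the time trend. Elsewhere the article uses within-person modelling as a first step and then compares with control, and the economic analysis may have been meant the same way. The objectives and the intention-to-treat statement point in that direction too. This stands as far as it goes: a before-after analysis is not established. But Secondary Outcomes does not state the second step, and its wording still conflicts with research question 2.

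A reader might infer several stronger things that the article does not support:
- **That the cost per QALY will have the wrong sign.** The reversal above needs both a baseline anchor and the assumed utilities.
- **That the reported decline would be charged to WTC.** That result is preliminary, is not given by arm, and concerns SF-12 mental health rather than SF-6D utility. The article itself says it is too early to judge the longitudinal course. It makes drift plausible and no more.
- **That only WTC is costed.** Implementation costs of the Tracker are also planned. The accurate point is that no usual-care cost is named.
- **That the control data are thrown away.** They are still collected. What is missing is their use as comparator in the stated economic analysis.

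Dropout is also not a fault peculiar to a within-person comparator, since it can bias a between-arm comparison as well. Finally, this is a secondary outcome, and the primary anxiety comparison is unaffected.

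**Conclusion.** The point holds as a contradiction between Secondary Outcomes and research question 2, together with an undefined Tracker and an absent control-arm cost. Condensation into an article does not explain it, because a different comparator is positively stated. Followed as written, the economic analysis does not answer the question the trial sets.

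Confidence is high for the mismatch. It is lower for the resulting bias, which depends on how the expected trajectory would be built. With one pre-randomisation SF-12 value, a participant's own data cannot supply an expectation that separates time trend or regression to the mean from a WTC effect. The figure of 0.0025 to 0.0125 QALY rests on an assumed linear drift of 0.01 to 0.05 and a baseline anchor. The size and sign in this trial are unknown.

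**What to change.** Rewrite the economic paragraph of Secondary Outcomes along these lines: incremental costs and SF-6D QALYs are the differences between randomised arms, WTC minus CAMH usual-care tools, analysed by intention to treat and adjusted for baseline utility; the acceptability curve is based on these differences. Details such as how QALYs are accumulated and how uncertainty is resampled can stay in the analysis plan. If the expected trajectory was meant to come from the control arm, say so explicitly in the same place.

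Add a control-arm delivery cost as a stated assumption with a range. The range is needed because Control and Limitations say usage in that arm will not be monitored, whereas Table 1 lists usual-care monitoring at weeks 6 and 26; those statements should be reconciled. Remove the Wellbeing Tracker from this comparison, or define what it is and its role.

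The cost is mainly wording. No new outcome data are needed. The price is wider intervals than a pre-post analysis would give, and one assumed control-arm cost.

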### Sample Size

The target sample size for the population survey and learning systems sample is 2000. This sample size will also allow for the estimation of the impact of the dashboard and app recommendations on score trajectories of the PHQ-9 and 7-item Generalized Anxiety Disorder Scale (GAD-7). Based on an estimated effect size of Cohen *d*=0.17 for changes in the PHQ-9 score and Cohen *d*=0.13 for changes in the GAD-7 score (based on the expected effects of the dashboard) [15], an expected dropout rate of no more than 35% [16], and population mean and SD estimates of PHQ-9 and GAD-7 scores [17,18], we estimate having a power of 0.90 and a type I error rate of 0.05 for detecting improvements in PHQ-9 and GAD-7 scores for subsamples with at least 1000 participants. Therefore, in this study, we will have a sample size of a total 2000 participants, with 1000 randomized to each group.

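### The power statement and one cost-effectiveness criterion rest on PHQ-9 change, but Table 1 schedules only PHQ-9 item 9 at screening and the PHQ-4 afterwards

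*Protocol article*

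**What the plan says.** Three parts of the protocol article bear on how depression is measured.

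- **Sample Size.** The sample is said to allow "estimation of the impact of the dashboard and app recommendations on score trajectories of the PHQ-9" and of the GAD-7. The assumed effects are "0.17 for changes in the PHQ-9 score" and "0.13 for changes in the GAD-7 score". The claim that follows covers both scales: "we estimate having a power of 0.90 and a type I error rate of 0.05 for detecting improvements in PHQ-9 and GAD-7 scores".
- **Secondary Outcomes, text.** Cost-effectiveness will also be estimated on reliable-change scores, one of which is "5 points on the PHQ-9"; the other is a 6-point change on the GAD-7.
- **Secondary Outcomes, Table 1.** The PHQ-9 appears in one row, on Day 1: "Screening assessments (PHQ-9^a^ item 9". The baseline row at week 0 names the GAD-7 and PHQ-4. The follow-up row reads "Biweekly short and long follow-up (GAD-7, PHQ-4, Current Substance Use, SF-12, and WSAS", and the last row "Final assessment (GAD-7, PHQ-4, current substance use, SF-12, and WSAS". The table notes define the PHQ-4 separately, as a 4-item questionnaire.

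Two other sections are relevant. Primary Outcomes and Statistical Analysis plan a multilevel model of anxiety and depression without naming a depression scale. Participant Withdrawal Criteria refers to suicidal thoughts at the long follow-ups in weeks 4, 8, 12, 16, 20 and 24 and names no instrument.

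**The concern.** A change score needs the same total at two or more times. The schedule provides one PHQ-9 item at one time. Followed as printed, it leaves one of the two scales in the power statement, and one of the two numerical reliable-change criteria, without data.

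The PHQ-4 does not fill the gap by itself, because the article gives no effect size, SD or change threshold for it. Any depression result on the PHQ-4 would therefore carry no stated power, and the 5-point criterion would have nothing to be applied to. Recruitment is reported as ongoing, and a questionnaire that was not given cannot be recovered later.

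**Working it through.** The core of the check is a comparison of instruments. The only arithmetic concerns what the remedies cost.

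**Step 1. Full PHQ-9 totals scheduled in Table 1**

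| Time | Depression measure listed | Full PHQ-9 total |
|---|---|---|
| Day 1 screening | PHQ-9 item 9 | no |
| Week 0 baseline | PHQ-4 | no |
| Weeks 2 and 4 | PHQ-4 | no |
| Week 6 | none listed (monitoring only) | no |
| Weeks 8-24 | PHQ-4 | no |
| Week 26 final | PHQ-4 | no |

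The PHQ-4 is named in three separate rows and has its own table note, so a single typing slip is unlikely.

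**Step 2. Quantities that need a full PHQ-9 total**

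- The PHQ-9 trajectory and d=0.17 in Sample Size need it at baseline and at least one later visit.
- The 5-point criterion in Secondary Outcomes needs it at two times.
- The GAD-7 trajectory and the 6-point GAD-7 criterion do not need it. The GAD-7 is listed at baseline, follow-up and week 26.
- The depression model names no scale, so it can be fitted to PHQ-4 data.

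**Step 3. Does the sample size depend on the PHQ-9?**

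For a fixed design, power and alpha, the required n is proportional to 1/d². The ratio of GAD-7 to PHQ-9 requirements is 0.17²/0.13² = 0.0289/0.0169 = 1.71. The GAD-7 is the more demanding of the two, so taking the PHQ-9 out of the power statement does not lower the required n.

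**Step 4. Power for PHQ-9 change if the scale is introduced only for new participants**

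Inputs: 2000 participants, 1:1 allocation, dropout up to 35% and d=0.17 (Sample Size); 453 participants so far (Abstract and Results). Assumptions: the 453 count toward the 2000 and have no PHQ-9 baseline; the comparison is between arms at two-sided alpha 0.05.

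- Remaining: 2000 - 453 = 1547, or 1547/2 = 773.5 per arm.
- Completers: 773.5 × 0.65 = 502.8, about 503 per arm.
- Power = Φ(d × √(n/2) - 1.96) = Φ(0.17 × √251.5 - 1.96) = Φ(2.696 - 1.960) = Φ(0.736) = 0.77.

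The article states 0.90 without naming the test or its sidedness. The gap between 0.90 and 0.77 should therefore not be read as the effect of losing the 453 alone. Whether 0.90 itself reproduces is a separate question on which this point does not depend.

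**The case against.** **Table 1 may be incomplete.** This is the strongest reply, and it stands in part. The withdrawal section implies that some suicidal-thoughts item is asked at weeks 4 to 24, yet Table 1 shows none after Day 1. Table 1 also merges short and long follow-ups into one row with one instrument list. Its week 6 column has no outcome scale, although Duration and Assessments places biweekly follow-ups from week 2 to week 24. The exclusion criterion refers to PHQ-9 scores rather than a single item. A reader might infer from Table 1 that no PHQ-9 total exists for anyone. The documents do not support that; they show only that none is scheduled. The full PHQ-9 may be in use, in which case the table is what needs correcting.

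**Anxiety is primary.** This also stands. Trial Design, Primary Outcomes and Statistical Analysis all put anxiety first, and the GAD-7 is collected. A reader might infer that the primary analysis is undermined, or that depression cannot be analysed at all. Neither follows. Beyond the sample size, PHQ-9 change is named only for an additional cost-effectiveness calculation.

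**The 5-point rule on the PHQ-4.** A reader might suppose that the rule will be carried over to the shorter scale. The article does not propose this, and it describes neither the item content nor the scoring of the PHQ-4, so no argument is built on it here.

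**An article condenses.** This does not remove the point. The article prints a schedule by instrument and visit, and what that schedule states disagrees with two other places in the same text.

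**Conclusion.** The contradiction is real and lies within the current text. As scheduled, no visit yields a full PHQ-9 total, so the PHQ-9 part of the power statement and the 5-point PHQ-9 criterion cannot be carried out as written, and the PHQ-4 has no effect size or change threshold in their place. The effect is limited to those two items. The GAD-7 primary trajectory, the GAD-7 criterion and the required sample size are untouched, and a PHQ-4 depression trajectory remains open.

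Confidence is high that the passages disagree. It is not high that PHQ-9 data are absent in practice, because Table 1 may be incomplete. The power of about 0.77 holds only under the assumptions listed with it. In particular, it is unclear whether the 453 belong to the 2000: they are reported as of August 2023, while the trial is dated from October 2023.

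**What to change.** Reconcile Participant Withdrawal Criteria, Sample Size and Secondary Outcomes with Table 1. Which change is needed depends on what is actually administered.

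1. **The full PHQ-9 is already given.** Correct Table 1 to show the visits. This costs one table edit.
2. **It is not given.** Choose one of the following.
   - Schedule the PHQ-9 at baseline, the long follow-ups (weeks 4, 8, 12, 16, 20 and 24) and week 26 for participants not yet enrolled. State that those already assessed with the PHQ-4 cannot contribute PHQ-9 change, and restate the PHQ-9 power for the participants who can. The cost is a form and schedule amendment, with at most nine further items at eight assessments (1 + 6 + 1), plus the reduced PHQ-9 sample.
   - Remove the PHQ-9 from the power statement and delete the 5-point criterion. Name the PHQ-4 depression items as the secondary depression outcome, stating which items and how they are scored. Base the reliable-change cost-effectiveness analysis on the GAD-7 alone. The cost is wording only, and every participant's data remain usable.

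Under either route, Table 1 should show which instrument provides the suicidal-thoughts check that the withdrawal section relies on, and at which visits.

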### Data Management and Availability

All data will be collected and managed in the REDCap electronic case report forms. This system is maintained on central CAMH servers, with data backed up daily, and is supported by the Research Informatics department. This will strengthen the data’s accuracy and maintain data quality. Only authorized personnel will monitor the completion of surveys, sending up to 3 reminder emails to participants who have not completed baseline surveys, up to 3 reminder emails to participants who have not completed follow-up surveys, and up to 3 reminder emails to participants who have not completed 6-month surveys.

The data sets will be stored on the secure CAMH server, and only for the minimum amount of time needed for fraud screening. Only trained research staff will have access to the data sets, and they will only use the merged data set for fraud screening purposes. As participants are screened, they will be entered into the screening log. Those deemed eligible will have their contact information, study ID number, and first name copied by research staff into the master linking log (a separate Excel [Microsoft Corp] file stored in a separate location from the fraud screening data). Once each round of fraud screening is completed, the merged data file will be securely destroyed. The original contact files may remain on the CAMH server to cross-check study IDs with the screening log, in the event that an ineligible individual contacts staff and inquiries about their eligibility. 

